## Abstract

**Introduction:**

Haemophilia is a rare, inherited disorder in which blood does not clot normally, resulting in bleeding into joints and muscles. Long-term consequence is disabling joint pain, stiffness, muscle weakness, atrophy and reduced mobility. The purpose of this proposed feasibility of a randomised controlled trial (RCT) is to test the feasibility of an age-appropriate physiotherapy intervention designed to improve muscle strength, posture and the way boys use their joints during walking and everyday activities.

**Methods and analysis:**

A small-scale two-centre RCT of a 12-week muscle strengthening exercise intervention versus usual care for young children with haemophilia will be conducted. Primary outcomes will be safety and adherence to the exercise intervention. Secondary outcomes will include recruitment, retention and adverse event rates, clinical data, muscle strength, joint biomechanics and foot loading patterns during walking, 6 min timed walk, timed-up-and-down-stairs, EQ-5D-Y, participants’ perceptions of the study, training requirements and relevant costs. Recruitment, follow-up, safety and adherence rates will be described as percentages. Participant diary and interview data will be analysed using a framework analysis. Demographic and disease variable distributions will be analysed for descriptive purposes and covariant analysis. Estimates of differences between treatment arms (adjusted for baseline) and 75% and 95% CIs will be calculated.

**Ethics and dissemination:**

The study has ethical approval from the London—Fulham Research Ethics Committee (17/LO/2043) as well as Health Research Authority approval. As well as informing the design of the definitive trial, results of this study will be presented at local, national and international physiotherapy and haemophilia meetings as well as manuscripts submitted to peer-reviewed journals. We will also share the main findings of the study to all participants and the Haemophilia Society.

Strengths and limitations of this studyThis study investigates the feasibility of a multicentre randomised controlled trial of a muscle strengthening exercise intervention versus usual care in children with haemophilia.The intervention to be studied has been coproduced by children with haemophilia, their parents and healthcare professionals.It is impossible to blind those in receipt and those delivering the intervention as to the group allocation, but we will blind the assessor as to group allocation.At the end of this study, we will not be able to answer the question ‘Does exercises help improve the long term health of children with haemophilia?’, but we will know whether such a study could be undertaken and the best way to deliver the intervention.

## Introduction

Haemophilia is a rare, inherited disorder in which blood does not clot normally. Repeated spontaneous and traumatic bleeding into joints and muscles is the result; the ankle joint being the most common.^1^ Long-term consequence is chronic arthropathy, a pattern of disabling joint pain, stiffness, muscle weakness, atrophy and reduced mobility.^2–4^ The introduction of prophylaxis with clotting factor concentrates has reduced the number of bleeding episodes experienced by children, changing their lifestyle and long-term outlook.^5 6^ However, evidence indicates that despite prophylaxis, boys still bleed one to two times per year, with relatively few bleeding episodes being required to initiate bone destruction, and in some cases, articular erosion is evident with no history of joint bleeding.^1 7–9^ Furthermore, children are more susceptible to blood-induced damage than adults and once established is progressive and irreversible.^10^

It is well established that muscle weakness is associated with haemophilic arthropathy in adults,^4^ and it is now becoming apparent that muscle strength is reduced in children, prior to the onset of clinical arthropathy.^11^ In a study of 10 adolescent and adult haemophiliacs with a history of unilateral knee bleeding, Falk *et al* found that strength of the knee extensors and flexors in haemophilic children was significantly weaker than those of the age-matched controls.^12 13^ More recently, Stephensen *et al* observed that despite normal clinical examinations and comparable levels of physical activity, young haemophilic boys with a history of ankle joint haemorrhage had significantly reduced dynamic muscle strength together with atrophy of the knee extensors, ankle dorsiflexors and plantarflexors when compared with age-matched and size-matched typically developing peers.^11^ Furthermore, muscle weakness of the leg is strongly correlated to muscle atrophy, reduced walking distances, slower ascent and descent of stairs, as well as reduced ankle joint motion, greater knee flexion motion and forces at the knee and ankle joint during walking.^14 15^

Therapeutic exercise is an important component of the management of other forms of arthropathy (eg, osteoarthritis, rheumatoid arthritis),^16^ and it would appear logical that exercise would be effective for people with haemophilia. There is growing evidence of the benefits of incorporating muscle strengthening exercise in their management of arthropathy.^17^ It is the view of clinicians that increases in muscular strength and postural control might improve motor performance and cardiovascular fitness, limit exaggerated end-range joint movement and promote optimal transfer of weight-bearing forces through joints, thereby minimising muscle imbalance, synovial impingement and associated haemarthroses or synovitis.^18^ However, there is a lack of evidence to support these assumptions. A recent Cochrane Review evaluating the safety and effectiveness of exercise for people with haemophilia reported four randomly controlled studies of an exercise intervention in children with the condition and concluded the studies were of low or very low quality, due to small sample sizes and potential bias.^17^ Furthermore, no paediatric study compared a muscle strengthening intervention to a control group or intervention without muscle strengthening exercises. Several studies compared two multicomponent exercise interventions that included broad muscle strengthening as well as treadmill walking and cycle ergometry, and it is not possible to determine the effect of muscle strengthening on muscle strength or its effect on physical function.^19 20^ Furthermore, preadolescent and adolescent boys aged between 10 and 14 years were included in these studies, and it is not known if the groups were matched for pubertal status.

Despite the apparent benefit, there is a lack of robust evidence to determine whether muscle strengthening exercise can improve or negatively affect outcomes for young children with haemophilia. The purpose of this proposed feasibility RCT is to test the feasibility of an age-appropriate physiotherapy intervention designed to improve muscle strength, posture and the way boys use their joints during walking and everyday activities.

## Methods and analysis

The protocol version for this feasibility study is V.2—19 December 2017. The Standard Protocol Items: Recommendations for Interventional Trials (SPIRIT) guidelines^21^ have been used to report the study protocol.

### Participants

Participants will be invited from two haemophilia centres. Twenty boys with severe or moderate haemophilia A or B with or without inhibitors on prophylactic treatment with coagulation factor concentrate, aged 6–11 years, will be recruited. Boys with or without symptoms of joint damage (evaluated using the Haemophilia Joint Health Score and Haemophilia Early Arthropathy Detection with Ultrasound score) will be eligible to participate. Exclusion criteria are as follows: von Willebrand disease, history of fracture or trauma to the lower limb, orthopaedic surgery, acquired brain injury or any other disturbance of the central nervous system, joint or muscle bleed in the lower limb in the past 6 weeks, presence of lower limb pain or unable to fully comply with verbal instructions.

Participants will be identified from each Haemophilia Centre’s database of registered patients. The parents or guardians of eligible participants will be approached initially by the principle investigator at each site via telephone to provide a brief verbal explanation of the research study and ask if they would be happy to receive a patient information sheet. Should they be interested in participating in the study they will receive, by post, the patient information sheet (one for parents and a separate age-appropriate version for children) at least 1 week prior to their next clinic appointment. This will allow for a ‘cooling-off’ period of a minimum of 1 week for the potential participants. The researcher will then be available for questions by telephone or at the participant’s next clinic appointment.

At their clinic appointment, the investigator will meet with the participant and parent/legal guardian to complete the consent form as appropriate. The investigator will further explain the study procedures, why they are being asked to consider including their child in this study and the associated risks and benefits of being included. They will then be given an opportunity to ask any further questions. The child/parent/ legal guardian will then be asked to confirm if the potential participant agrees to take part in the study. If consent is agreed, a parental consent form will be completed by the parent/guardian and a copy will be provided. If at any point during the study process the parent/guardian does not consent to inclusion in the study, then any data collected will be destroyed. Any decision to refuse or withdraw from the study will in no way influence the services that they receive. Once the child’s parent/guardian has given consent, the child must also indicate that they do not object to participating in the research activity. This participant ‘assent’ will be sought.

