### Usual care

Participants will continue to receive their usual care as recommended and prescribed by the haematologist, physiotherapist and other members of the healthcare team. This will include factor concentrate treatment, any physiotherapy or surgical intervention or advice that is recommended by the clinical care team. There are currently no standardised treatment recommendations for children without apparent joint damage. The researchers will not make or initiate any changes to routine treatment. Any change to or initiation of new treatment or intervention will be recorded and the treating clinician will determine whether it is appropriate for the participant to continue in the study. Participants will be provided with a diary to record participation in physical activities, including type, time and intensity. Participants will be telephoned weekly to encourage dairy completion. On return of the diary every 2 weeks, participants will be provided with a gift voucher.

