### Outcome measures

Primary outcome measures are as follows:Safety will be evaluated using annualised bleeding rates, coagulation factor usage (what the patient actually administers and records on their routine electronic diary) and reported adverse events and reactions associated with the intervention. Association with symptoms of joint disease (Haemophilia Joint Health Score and Haemophilia Early Arthropathy Detection with Ultrasound score) will be evaluated.Adherence to the exercise intervention will be evaluated by the number of exercise session completed as a percentage of the prescribed exercise sessions. Data will be extracted from participant diaries.

Secondary outcome measures are as follows:Recruitment rate determined as the participants who volunteer to participate in the study as a percentage of those that are invited/eligible.Willingness to be randomised; evaluated at the end of study through semistructured interviews that will be audio-recorded and be transcribed by a member of the research team.Participant’s acceptability of the trial and intervention: using semistructured interviews, conducted at the completion of the study, the participants will be asked their views on acceptability of the trial and intervention, recruitment and exercise adherence. The interview will be audio-recorded and transcribed by a member of the research team.Training required to deliver the intervention and collect outcome data at study visits: using semistructured interviews, conducted at the completion of the study, the physiotherapists will be asked their views on acceptability of the trial and intervention, recruitment and exercise adherence. They will also be asked about the training requirements for delivering the intervention as well as the appropriateness of the outcomes piloted in terms of training, length of time to complete and clinical value of the data. The interview will be audio-recorded and transcribed by a member of the research team.Haemophilia Joint Health Score (HJHS)—a clinical examination of swelling, muscle atrophy, strength, joint crepitus, range of motion and pain at the ankle, knee and elbow joints. The HJHS is a standardised multi-item assessment, currently used in clinic as part of routine care to record musculoskeletal health.^22^

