### Analysis methods

Recruitment, follow-up, safety and adherence rates will be described as percentages. Participant diary and interview data will be analysed to identify factors that influence these rates and acceptability of the trial using a framework analysis. Interview data from physiotherapists will be analysed using a framework analysis to determine training required to deliver the intervention and collect outcome data. Feasibility of collecting healthcare cost data will be explored along with the resource consequences. Costs will be analysed and reported using descriptive statistics. Demographic and disease variable distributions will be analysed for descriptive purposes and covariant analysis. Walking variables will be normalised to leg length and muscle strength to body mass. Group mean and SD (median and interquartile range where appropriate) will be calculated and reported. Change from baseline data will be compared between groups at all study time points using analysis of covariance with baseline as a covariate and a factor for centre. Estimates of differences between treatment arms in the changes from baseline (adjusted for baseline) and 75% and 95% CIs will be calculated. Group mean and SD (median and interquartile range where appropriate) will be calculated preintervention and postintervention. These data will allow us to estimate the potential effect of the intervention and provide estimates of variability to inform the sample size required for a full RCT, as well as to refine the outcome measures by evaluating their responsiveness to changes in musculoskeletal health.

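### The rule that destroys collected data when consent is not given would, on its natural reading, erase withdrawn boys' records from both primary outcomes

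*Protocol article*

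**What the plan says.** The rule is in the consent paragraph of the protocol article, under Participants. It applies at every stage of the study: if the parent or guardian "does not consent to inclusion in the study, then any data collected will be destroyed". The sentence after it reads "Any decision to refuse or withdraw from the study will in no way influence the services that they receive". No exception is made for safety events or session counts.

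The abstract states "Primary outcomes will be safety and adherence to the exercise intervention". Under Outcome measures, "Safety will be evaluated using annualised bleeding rates, coagulation factor usage" and reported adverse events and reactions. Adherence is sessions done as a percentage of sessions prescribed, taken from the participant diaries. Under Intervention, the same diary is where families in the exercise group record adverse events. Under Analysis methods, "Recruitment, follow-up, safety and adherence rates will be described as percentages", and diary and interview data are to be used to find out what influences those rates.

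Under Management and oversight, site investigators report adverse events and reactions, and the chief investigator notifies the Research Monitoring Committee (RMC). The article does not say whether those records are kept when a boy's data are destroyed.

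**The concern.** A feasibility trial learns much of what it needs from the participants who leave. If a family withdraws and the diary is destroyed, the boy's session count and his diary-recorded events can no longer enter the two primary outcomes. Their percentages would then describe only the boys who stayed.

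If leaving is related to harm, burden or poor adherence, that is selective loss in the primary outcomes. It also works against the stated aim of explaining what drives safety, adherence and follow-up. With about 10 boys per arm, one or two withdrawals are enough to change the message. Destroyed data cannot be recovered by any later analysis.

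**Working it through.** The plan gives no dropout rate and no calculation behind its sample size, so there is no stated figure to reproduce. The check has two parts: how the rule reads, and what it could do to the percentages.

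**Reading the rule.** Two features favour coverage of withdrawal after randomisation. The rule applies throughout the study, and it presupposes that data already exist. The following sentence then treats refusal and withdrawal together. One feature points the other way: the operative words concern not consenting to inclusion, in a paragraph mainly about the consent visit. The broader reading is the more natural one, but it is not certain.

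**Inputs from the article.** Twenty boys (Participants) allocated 1:1 (Study design): 20 × 1/2 = 10 per arm. Prescribed sessions: 24 (Intervention).

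**Assumptions, not from the article.** Stayers complete 85% of sessions (0.85 × 24 = 20.4). Withdrawers complete 0–40% of the full 24 (0 to 9.6 sessions).

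**Adherence.** With *w* of 10 boys withdrawing and a withdrawer's adherence *a*:

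- data kept: [(10 − w) × 85 + w × a] / 10
- data destroyed: 85, whatever *w* is

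| Withdrawers | Kept, a = 0 | Kept, a = 40 | Destroyed |
|---|---|---|---|
| 1 | (9×85 + 0)/10 = 76.5% | (9×85 + 40)/10 = 80.5% | 85% |
| 2 | (8×85 + 0)/10 = 68.0% | (8×85 + 80)/10 = 76.0% | 85% |
| 3 | (7×85 + 0)/10 = 59.5% | (7×85 + 120)/10 = 71.5% | 85% |

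Under these assumptions the overstatement runs from 85 − 80.5 = 4.5 points to 85 − 59.5 = 25.5 points.

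**Safety, as the proportion with a bleed.** Suppose 3 of 10 exercise boys bleed (30%) and two boys withdraw:

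- both had bled: 1/8 = 12.5%
- one had bled: 2/8 = 25%
- neither had bled: 3/8 = 37.5%

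The direction depends on who leaves. A simple proportion is used for illustration; the article also names annualised bleeding rates and factor usage.

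**How likely is at least one withdrawal?** With assumed per-boy probability *p*, the chance among 10 boys is 1 − (1 − p)^10:

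- p = 5%: 40%
- p = 10%: 65%
- p = 20%: 89%

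**The case against.** The strongest objection is to the reading. The authors use the word withdraw in the next sentence but not in the destruction rule, which could therefore be meant for families who decline at the outset. This stands as a reason for caution. But a rule that runs throughout the study and speaks of data already collected is hard to confine to initial refusal. If refusal is all that was meant, the text should say so.

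A second objection is that adverse events have another route, through the site and chief investigators to the RMC, which has an independent chair. This also stands in part: events already notified would be known to that committee, so it would be wrong to say that such harm disappears. What is open is whether those reports survive destruction and count in the published safety figures.

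A third is that erasure on a family's decision is an ethics choice, made under ethics approval. That is fair. The fix keeps erasure available on request and changes only the default.

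Three stronger inferences are not supported:

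- **That a treatment change also removes data.** Under Usual care, a change "will be recorded and the treating clinician will determine whether it is appropriate for the participant to continue in the study". This leaves continuation open and orders no deletion. A boy taken out might miss later visits, but that clause is not part of the error.
- **That the follow-up percentage is biased as well.** It needs only counts of boys randomised and assessed. Nothing says that the fact of randomisation or withdrawal is erased, and a withdrawal would lower the rate.
- **That the bias must favour a safe and feasible conclusion.** The article gives no reasons for withdrawal, and the bleed example moves both ways. Nor does it state a progression threshold that a distorted percentage would trigger.

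**Conclusion.** The concern holds for the destruction rule under Participants. This is a stated rule, not a detail left to a fuller document. On its natural reading it would take withdrawn boys' diary data out of both primary outcomes.

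Its size is conditional. In the illustration, adherence is overstated by 4.5 to 25.5 points when one to three of ten boys withdraw. That requires withdrawers to have done fewer sessions than stayers, which is plausible but assumed. For safety, a true 30% could be reported as anything from 12.5% to 37.5% after two withdrawals, so the defect is distortion of unknown direction. If the rule was meant for initial refusal only, the fault is one of wording and the distortion does not arise.

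**What to change.** Amend the Participants text, the information sheet and the consent form as follows:

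- Data collected up to withdrawal are kept in coded form and analysed, unless the family explicitly asks for erasure. Families are told this before consenting.
- Adverse events and session counts up to withdrawal are retained on the same terms.
- Adherence and safety are reported with all randomised boys in the denominator (for adherence, all those randomised to exercise), together with the number, timing and, where offered, reason for withdrawals. Any erasures on request are counted.
- The rule is reconciled with adverse event reporting under Management and oversight, stating whether events already notified to the RMC are kept and reported.

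The cost is an ethics amendment covering these documents, with no extra participants or visits. It should be in place before any family withdraws, because data destroyed under the present wording cannot be restored.

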### Study design

Following written informed consent and screening of eligibility criteria, randomisation of eligible participants for the study will be performed with the online randomisation service http://sealedenvelope.com/. Utilising the secure, centralised and independent service, participants will be randomly allocated into one of the two groups (treatment group 1 will receive a 12-week muscle strengthening exercise intervention; treatment group 2 will receive usual physiotherapy care for 12 weeks) on a ratio of 1:1. Allocation will be stratified by centre to ensure the same numbers of participants at each site are allocated to the two groups. The unblinded principal investigator at each site will be issued with a password to access the service to create a new randomisation for the study participants. Those allocated to treatment group 2 will be offered the intervention after their end of study follow-up assessment. Data will be collected prior to and immediately postintervention (figure 1).

